#### Acupuncture Group

In this study, acupuncture treatment will follow a standardized protocol based on traditional Chinese medicine principles, expert consensus, and clinical experience [39]. Participants will receive acupuncture in a private room, with the affected knee being the sole treatment focus for those with osteoarthritis symptoms. Sterile, single-use needles (0.25 mm gauge, 25‐40 mm in length, Hwato) will be used.

Before the study, all acupuncturists will undergo comprehensive training on standardized procedures, including precise acupoint location and needle manipulation techniques. The acupuncture protocol will involve five core acupoints: Dubi (ST35), Neixiyan (EX-LE5), Ququan (LR8), Xiyangguan (GB33), and an Ashi point, with up to 3 supplementary points chosen based on the affected meridian (Figure 2). Ashi points are defined as tender points within the knee joint region, marked by sensations of soreness, distension, or pain.

**Figure 2. F2:**
[figure not shown]
Location of acupoints for the acupuncture group. Core acupoints: Dubi (ST35), Neixiyan (EX-LE5), Ququan (LR8), and Xiyangguan (GB33).

Achieving the De qi sensation, a combination of soreness, numbness, distension, and heaviness, will be required for every session. Participants will receive two 30-minute acupuncture sessions per week for 6 weeks, totaling 12 sessions. Sessions will be spaced at least 48 hours apart.

#### Tuina Group

##### Overview

Participants randomized to the Tuina intervention arm will undergo integrated acupuncture and Tuina in private treatment settings, following the same standardized acupuncture protocol as that administered in the acupuncture group. The Tuina protocol will include manual therapy, covering Tuina techniques applied to both sides of the affected limb, as well as passive range-of-motion exercises for the knee joint [40,41].

To ensure consistency and reproducibility across all sessions and practitioners, the core Tuina manipulations (rolling, kneading, and pressing) are formulated primarily according to the *Tuina Therapy–14th Five-Year Plan Textbook* and previous research and will be executed with a fixed order listed below.

##### Step 1: Rolling in Supine Position

The practitioner’s right hand should exert force on the dorsal ulnar side, stick it to the anterior thigh, and roll back and forth through continuous movement of wrist flexion and extension and forearm pronation and supination. The frequency will be approximately 120 times per minute. The manipulation will be repeated from top to bottom 3 to 5 times [42].

##### Step 2: Kneading and Pressing Technique

This step focuses on the application of kneading and pressing techniques.

Kneading: use the left or right thrusting thread or the fingertip of the thumb to perform rhythmic spiral movements.Pressing: using their thumb or index finger, the physician should press the corresponding acupoints with the middle finger or index finger for 5 to 10 seconds.

Both kneading and pressing techniques will be applied to Heding (EX-LE2), Neixiyan (EX-LE4), Dubi (ST35), Yanglingquan (GB34), Yinlingquan (SP9), Xuehai (SP10), and Ashi points, taking the patient’s feeling of soreness, distension, and pain as the degree of tolerance without exerting too much force, aiming to elicit the De qi sensation, which is indicative of effective manipulation. Following this, patients will transition to a prone position.

##### Step 3: Rolling in Prone Position

The practitioner will then use the back of the hand to perform rolling motions over the posterior thigh, popliteal fossa, and posterior leg. The operational standard of rolling is identical to the rolling technique in step 1 (Figure 3). This sequence aims to relax the muscles and stimulate the collaterals.

**Figure 3. F3:**
[figure not shown]
Demonstration of Tuina. (A) Initially, patients will be positioned supine, with the practitioner standing beside them. The practitioner will use the back of the hand to perform rolling motions over the anterior thigh. (B) Subsequently, kneading and pressing techniques will be applied to key acupoints, including Heding (EX-LE2), Neixiyan (EX-LE4), Dubi (ST35), Yanglingquan (GB34), Yinlingquan (SP9), Xuehai (SP10), and Ashi points. (C) The practitioner will then use the back of the hand to perform rolling motions over the posterior thigh, popliteal fossa, and posterior leg. (D) Finally, one hand will be used to apply pressure to the knee joint, while the other hand holds the ankle joint to facilitate passive flexion and extension exercises for the lower limbs for 1 min.

##### Step 4: Kneading and Passive Joint Manipulating

This step combines kneading with passive joint manipulation.

Kneading: The thumb will be used to apply pressure from the posterior thigh to the knee joint, whereas the other 4 fingers and the palm help stabilize the thigh.Passive joint manipulating: When one hand is manipulating the kneading technique, the other hand holds the ankle joint to facilitate passive flexion and extension exercises for the lower limbs for 1 minute.

Kneading and pressing techniques will be applied to Weizhong (BL40) and Chengshan (BL57). In total, participants will receive two 30-minute sessions per week for 6 weeks, totaling 12 sessions, with a minimum interval of 48 hours between treatments.

### Follow-Up

Upon completion of the 6-week intervention period, all patients will immediately transition into a 12-week unsupervised follow-up phase. At the end of the 18-week clinical period, patients with KOA will undergo assessments for all clinical evaluations, with the exception of except for the multi-MRI outcomes.

### Multi-MRI Examination Procedure

Multi-MRI data will be acquired using a 3.0-T magnetic resonance scanner (SIEMENS MAGNETOM Verio syngo MR B17), equipped with a 32-channel phase-array head coil, at the Institute of Science and Technology for Brain-Inspired Intelligence, Fudan University.

Before the magnetic resonance imaging (MRI) scan, participants will undergo a pre-MRI evaluation procedure, which includes instructions to rest for 10 minutes, relax, and maintain calmness throughout the session. During the scan, participants will be requested to close their eyes, wear earplugs, keep their heads stationary, remain relaxed and awake, and avoid thinking of anything specific.

The imaging protocol will include the following steps:

High-resolution T1-weighted image: A spin-echo sequence will be used to acquire a transverse sagittal scan with a flip angle of 9°, a repetition time (TR) of 1900 ms, an echo time (TE) of 2.93 ms, a field of view of 256×256 mm², 160 slices, and a slice thickness of 1 mm.Diffusion tensor imaging (DTI): DTI will be performed using axial DTI mapping sequences with a TR of 10,000 ms, a TE of 89 ms, a matrix size of 240×240, a slice thickness of 2 mm, B-values of 0 and 1000 s/mm², and 30 directions.Blood oxygenation level–dependent resting-state functional imaging: An echo-planar imaging sequence will acquire blood oxygenation level dependent–resting-state functional images with a coronal axial scan, 33 slices, a slice thickness of 4 mm, a TE of 30 ms, a TR of 2000 ms, a field of view of 220×220 mm², a voxel size of 3.4×3.4×4.0 mm³, a flip angle of 90°, and a scan duration of 8 minutes and 8 seconds, resulting in 240 volumes.

Following the MRI procedure, participants will be given an additional 5-minute rest period and may leave if they experience no discomfort.

### Outcome Measurements

#### Assessment Tools and Schedule

Clinical outcomes will be evaluated using 2 self-report questionnaires, 4 instrument-based indicators measured at baseline and after 6 weeks of treatment, and multi-MRI data. At the conclusion of the full 18-week clinical period, all clinical assessments, excluding multi-MRI outcomes, will be performed. The responses will provide valuable information on pain levels, sensory experiences, emotional states, and overall quality of life.

#### Primary Outcomes

The VAS score is based on a 10-cm long straight line, with the starting end marked as 0 points, indicating no pain, and the end marked as 10 points, indicating unbearable severe pain. Patients will select a point on the line that represents their current level of pain. A lower total score indicates reduced pain severity, reflecting the effectiveness of the interventions. This VAS is distinct from the VAS component within the short-form McGill Pain Questionnaire (SF-MPQ), which is used solely for screening purposes and for baseline characterization.

#### Secondary Outcomes

##### Short-Form McGill Pain Questionnaire

The SF-MPQ will be used to assess the multidimensional experience of pain. It consists of 2 primary components.

###### Descriptive Pain Rating

This component comprises a list of 15 pain descriptors, categorized into 11 items evaluating sensory qualities of pain (eg, throbbing and shooting) and 4 items evaluating affective qualities (eg, tiring and fearful). Each descriptor is rated on an intensity scale ranging from 0 (none) to 3 (severe). The scores are summed to yield a sensory score (range 0‐33), an affective score (range 0‐12), and a total pain rating index (range 0‐45).

###### Present Pain Intensity

The present pain intensity is a single-item, 6-point verbal rating scale (0=no pain, 5=excruciating) that provides a global assessment of current pain intensity [43].

The pain intensity scores derived from the SF-MPQ will not be used as outcome measures in the longitudinal analysis.

### Pain Threshold

Pain threshold will be assessed at specific knee points—EX-LE02 (Heding), EX-LE04 (Neixiyan), EX-LE05 (Xiyan), and the area beneath the tip of the patella—using a pressure algometer. This measure will evaluate the sensitivity to mechanical pressure pain in patients with KOA [44,45].

### Muscle Tension

Muscle tension will be assessed in the quadriceps and gastrocnemius muscles, providing insights into muscle stiffness in patients with KOA [46].

### 10-Meter Walking Test

The 10-meter walking test (10MWT) will assess walking speed by timing the patients over a 10-m distance, with a focus on the middle 6 m to account for acceleration and deceleration. The test will begin when the toe of the leading foot crosses the 2-m mark and will end when the toe crosses the 8-m mark. Three trials will be conducted, and the average time will be recorded.

### Western Ontario and McMaster Universities Arthritis Index

The Western Ontario and McMaster Universities Arthritis Index (WOMAC) questionnaire will evaluate symptoms of KOA in 3 domains: pain (5 questions), stiffness (2 questions), and functional limitations during daily activities (17 questions) [47].

### Clinical Efficacy

Clinical efficacy will be categorized into 4 levels: cure, markedly effective, effective, and ineffective [48].

Cure: complete resolution of pain and symptoms, with normal joint activityMarkedly effective: resolution of pain and symptoms, with no limitation in joint activityEffective: significant reduction in pain and symptoms, with slight joint activity limitationIneffective: no significant improvement in pain, symptoms, or joint activity

### Multi-MRI Outcomes

#### Functional Imaging

Functional connectivity analysis will be used to assess brain network activity and interregional communication, highlighting potential neural mechanisms underlying pain perception and motor function in KOA.

#### Diffusion Imaging

Fractional anisotropy and mean diffusivity will be measured to assess white matter (WM) integrity, providing insights into neural pathway alterations in patients with KOA.

#### Structural Imaging

GM density, cortical thickness, and volumes of subcortical nuclei will be evaluated to investigate brain structural changes related to KOA.

### Safety Evaluation and Adverse Events

Participant safety will be actively monitored throughout the trial. At each treatment session and assessment visit, practitioners will systematically inquire about and record any adverse events (AEs). The following treatment-related AEs will be proactively monitored:

For acupuncture: significant needle pain, bleeding, hematoma or bruising (>2 cm), dizziness or fainting, and local infection [49]For Tuina: transient (>24 h) increases in pain, significant bruising, skin irritation, and unexpected joint discomfort [41]General: any other unexpected AE reported by the participant [42]

All AEs will be recorded in the case report form (CRF) with details on severity, duration, action taken, and outcome. The causality relationship to the intervention will be assessed by the investigator. The incidence and type of AEs will be summarized and compared between the 2 treatment groups as a key safety outcome. All AEs will be managed, recorded, and reported in accordance with the study protocol and the requirements of the Ethics Committee.

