### Blinding

This clinical trial will implement blinding for assessment to minimize potential biases. Statistical analysts will be blinded to participant recruitment, allocation, and treatment details to ensure the integrity and reliability of the study results. They will not have access to raw data until after the data collection process is completed and quality control measures are in place.

Due to the nature of Tuina and acupuncture interventions, achieving full blinding of patients and therapists is not feasible [37]. To minimize potential bias, therapists will not be involved in participant information collection, assessment, or subsequent data analysis. They will also refrain from disclosing information regarding the specific benefits or risks of the treatments to patients [38]. Additionally, to mitigate bias, outcome assessors and statisticians will remain blinded to group allocation throughout the study.

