### Data Management

Baseline data will be collected using CRFs, which will include clinical observations, outcome measures, AEs, and safety evaluations. Outcome assessors, who are independent of the data management team, will ensure impartiality in evaluations, completing forms based on anonymous participant identifiers to maintain blinding. Completed CRFs will be entered into a Microsoft Excel database by 2 independent data administrators who are blinded to group allocations and trained in data monitoring. An independent data manager will oversee data entry into the International Traditional Medicine Clinical Trial Registry.

Data will be stored securely in both physical and digital formats, with access limited to the data manager. Upon trial completion, anonymization procedures will be implemented to preserve participant confidentiality, and an independent data analyst will perform statistical analysis on the anonymized data, ensuring objectivity and transparency.

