This study used multi-MRI technology to explore the central analgesic brain mechanisms of Tuina intervention for KOA. This approach was chosen due to its advantages of high spatial resolution, absence of radiation, fast imaging speed, and noninvasiveness [63-65], enabling the assessment of brain GM structure, brain function, and WM integrity. KOA pain may be associated with morphological changes in subcortical structures and nuclei, representing part of the neuroimaging pathogenesis [66,67]. DTI can be used to quantify microstructural and macrostructural changes in WM [68]. Functional magnetic resonance imaging allows for in-depth analysis of patients’ pain perception and brain regulatory mechanisms for motor control. It is widely applied in research on the central mechanisms of Tuina analgesia [69-73] and has preliminarily identified functional changes in key brain regions, such as the amygdala, hypothalamus, nucleus accumbens, and hippocampus [74-76].

Current research has confirmed that both acupuncture and Tuina can improve clinical symptoms in patients with KOA, such as pain and dysfunction. The onset of clinical efficacy may be related to improvements in brain functional activity [40,62,77-81]. However, there is a lack of comprehensive, multidimensional research integrating brain GM structure, WM structure, and brain functional behavior for the combined treatment of KOA with Tuina and acupuncture.

The study’s extended follow-up period, including assessments at 12 weeks posttreatment, enhances its design by providing insights into the long-term effects of Tuina and acupuncture for KOA. Rigorous blinding protocols for outcome assessors and statisticians further ensure the reliability and validity of the findings. Unified training for all practitioners and assessors promotes consistency in intervention delivery, data collection, and analysis, thereby enhancing methodological robustness [82].

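### The protocol contradicts itself on who collects adverse events, and it lists the prompted events by modality, so the between-group safety comparison is open to unequal ascertainment

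*Protocol article*

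**What the plan says.** Three sections of the protocol article bear on who collects adverse events.

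- **Blinding.** It states that "achieving full blinding of patients and therapists is not feasible" and, as a safeguard, that "therapists will not be involved in participant information collection, assessment, or subsequent data analysis". Outcome assessors and statisticians are to stay blinded throughout.
- **Safety Evaluation and Adverse Events.** It states that "practitioners will systematically inquire about and record any adverse events (AEs", at every treatment session and every assessment visit. Causality is judged by the investigator.
- **Data Management.** "Baseline data will be collected using CRFs, which will include clinical observations, outcome measures, AEs, and safety evaluations". The same paragraph has outcome assessors completing forms under anonymous identifiers so that blinding is kept.

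The safety section then names the treatment-related events to be monitored proactively, in three groups:

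- acupuncture, five items: needle pain, bleeding, hematoma or bruising above 2 cm, dizziness or fainting, local infection;
- Tuina, four items: pain increase beyond 24 hours, bruising described only as significant, skin irritation, unexpected joint discomfort;
- general: other unexpected events that the participant reports.

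The use of the data is explicit: "The incidence and type of AEs will be summarized and compared between the 2 treatment groups as a key safety outcome".

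**The concern.** A between-group comparison of harms needs the same questions, the same definitions and the same kind of questioner in both arms. The text secures none of these.

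The people who ask and record know the allocation because they deliver the treatment, and the Blinding section says they will not have that role. The prompts are organised by treatment. Acupuncture prompts suit everyone, while Tuina prompts most naturally suit one arm. Two of the Tuina items, a pain flare and joint discomfort, can occur in any patient with knee osteoarthritis. If staff ask about them mainly where Tuina is given, the Tuina arm will show more events for that reason alone. An unblinded recorder could also shift the count in either direction.

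At stake is the interpretation of the safety comparison. The primary VAS analysis is not affected by this route.

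**Working it through.** **1. Are practitioners the same people as therapists?** The Tuina Group overview uses the word for those giving treatment: "To ensure consistency and reproducibility across all sessions and practitioners, the core Tuina manipulations (rolling, kneading, and pressing) are formulated". The step-by-step Tuina instructions do the same. The Discussion names them separately from assessors: "Unified training for all practitioners and assessors promotes consistency in intervention delivery, data collection, and analysis". So the practitioners who record adverse events are the unblinded treatment providers.

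**2. Setting the sections side by side.**

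| Section | Who collects | Blinded? |
|---|---|---|
| Blinding | not therapists | therapists are unblinded |
| Safety Evaluation and Adverse Events | practitioners, at every session and assessment visit | no |
| Data Management | outcome assessors complete forms; the case report forms include adverse events | yes |

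The first two rows contradict each other. The third fits the first but not the second. Table 1 places adverse events at weeks 6 and 18, and its footnote allows recording at any time, but neither says who records. Treating staff are the natural recorders during sessions. At week 18 that reason has gone: the Follow-Up section describes 12 unsupervised weeks after treatment, and the clinical outcomes are assessed at that visit by blinded assessors.

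**3. Counting the prompts.** There are 5 acupuncture items and 4 Tuina items. Bruising is on both lists, so there are 5 + 4 − 1 = 8 distinct types, of which 3 are on the Tuina list only. Both arms have 12 sessions, so the number of occasions for asking is equal. Any asymmetry lies in what is asked and how it is defined.

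**4. Size.** The protocol gives no adverse event rate and no safety power, so there is no stated figure to reproduce. The following is an illustration on assumed inputs.

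- *r*: true risk of a Tuina-list event, equal in both arms, assumed 10% to 40%.
- Detection in the Tuina arm: assumed complete.
- *d*: detection in the acupuncture arm, assumed 30% to 70%.
- 30 per arm, from Sample Size Calculation, ignoring dropout.

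Apparent risk difference = *r*(1 − *d*); apparent risk ratio = 1/*d*.

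- Smallest: 0.10 × (1 − 0.70) = 3 percentage points, ratio 1/0.70 = 1.4.
- Largest: 0.40 × (1 − 0.30) = 28 percentage points, ratio 1/0.30 = 3.3.
- Probability of Fisher's exact P < .05 (test assumed): 1% to 62% over this grid, against 1% to 3% with equal detection.
- With *d* = 1 the difference is 0.

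A count by item shows the same dependence on detection. Assume 5% per item, independent items and 8 distinct types. The Tuina arm shows 1 − 0.95^8 = 33.7%. The acupuncture arm shows 1 − 0.95^5 = 22.6% if the three unlisted types are never picked up, 1 − 0.95^5 × 0.975^3 = 28.3% if half are, and 33.7% if all are. The gaps are about 11, 5 and 0 points.

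**The case against.** A reader might infer that the Tuina group is asked about nine kinds of event and the control group about five, and that the comparison is therefore biased. The text does not say so. It tells practitioners to inquire about any adverse event, adds a general category, and nowhere says that Tuina items are withheld from the acupuncture arm. Nine also counts bruising twice. This part of the objection stands: what is shown is an exposure to bias. It does not remove the point, because the general category depends on what the participant reports, which is weaker than a prompt.

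A reader might also infer that adverse event entries on the case report form will unblind the assessors. The article does not describe the form's layout or say that assessors see practitioners' entries when they score outcomes. That is detail a full protocol may settle, and the point does not rest on it. Nor does Data Management say outright that assessors complete the adverse event pages, so the conflict with that section is looser than the one between Blinding and Safety Evaluation and Adverse Events.

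Asking about harms at each session is ordinary safety practice for treating staff, and short-lived events such as dizziness or needle pain would be lost if everything waited for weeks 6 and 18. This stands, and it argues for keeping the session records. Patients are unblinded whoever asks, as the limitations section accepts. This also stands: the remedy reduces the bias but cannot remove it.

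**Conclusion.** The point holds in two parts.

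First, the statements on who collects adverse events do not agree and must be reconciled. This rests on the text alone.

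Second, the modality-specific prompts and the two bruising definitions leave a comparison that the protocol calls a key safety outcome open to differential ascertainment. The lists would most likely raise the apparent count in the Tuina arm; unblinded recording could act either way.

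The size is unknown. The range of 3 to 28 points depends wholly on the assumed risks and detection rates, and the effect is nil if all items are asked in both arms. It would go too far to say that the adverse event difference cannot be interpreted, since the documents do not show that the arms will be asked different questions. The matter should be corrected before recruitment opens, but it does not touch the primary efficacy inference.

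**What to change.** - Use one adverse event checklist holding all the listed items, with a single bruising definition chosen by the sponsor. Ask it of every participant in both arms at the same sessions and visits.
- Have the existing blinded assessors administer it at the week 6 and week 18 assessment visits, after outcome scoring, so that an answer that reveals allocation cannot influence the scores.
- Keep practitioners' session-level records, on a separate form, for immediate safety and for short-lived events.
- Amend the Blinding section to state that exception, and align Safety Evaluation and Adverse Events and Data Management with it.
- If the lists stay as they are, describe the between-group comparison as open to ascertainment bias.

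The cost is a minor redesign of the case report form and a few more questions per visit, with no extra staff. The Results section says recruitment is not yet open, so this can be done in time. Some bias will remain because patients know their treatment, and their answers may still reveal allocation to an assessor.
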